**3.3 Planning in Health Services for Chronic Disease Care.**

The convergence of several developments in South Africa, and in particular the Western Cape, has created the opportunity for building an integrated model of healthcare delivery for CD involving collaboration between community, health services and local institutions (Figure 1). First, the National Health Act requires that communities become involved in the programme of care offered by the local health service. Second, the Western Cape Provincial Government has responded to this requirement through a unique commitment to an enhanced community health worker programme in chronic diseases. The Western Cape DoH has clearly articulated this approach in its strategic plan called the Healthcare 2010 Plan ([www.capegateway.gov.za](http://www.capegateway.gov.za)). Third, members of UCT and other regional institutions, who have developed and are implementing an integrated care model for nurses on chronic respiratory and infectious diseases, have been asked to expand this model to include chronic diseases. The commitment of the Western Cape Government to put in place integrated care guidelines for chronic disease management in 2011 gives us a unique opportunity to develop a research plan evaluating the impact of such a decision that will have widespread implications in the rest of South Africa and potentially other partner countries in the region such as Tanzania.

**3.4 Integrated Primary Care Model for Chronic Diseases proposed by the Chronic Disease Initiative in Africa (CDIA)**

The CDIA is a recently launched chronic disease initiative of Universities in the Western Cape, the MRC, Tanzanian and US collaborators. The CDIA proposes an integrated model for primary care for CD based on the World Health Organisation recommendations outlined in the publication ‘Innovative Care for Chronic Conditions (ICCC) (WHO 2002) (Figure 1). The model aims to strengthen and broaden the health care team by providing tools that improve the effectiveness of care and by mobilising community support and patient involvement in their own care. This protocol addresses three aspects of the integrated primary care model.

The first aspect is to calibrate and validate a feasible cost-effective tool for identifying patients at high risk for cardiovascular disease (CVD) without laboratory testing. The second aspect will be a pragmatic trial testing the effectiveness of our integrated care guideline training program for health care providers in the primary care setting. Finally, a cardiovascular disease prevention policy model will be developed that can be used to evaluate the cost-effectiveness of the integrated care guideline programme through changes in process measures and/or risk factors. Further, the model will be available to forecast future CVD burdens and evaluate the cost-effectiveness of future interventions that prevent CVD or reduce its risk factors.

**Figure 1: Integrated Primary Care Model for Chronic Diseases**

Patients

Clinic-based Staff

Community

CHW

CHW

Managers

Screening in the community with non-lab tool

Training to lead therapeutic groups and support individual patients

Guideline-based training in diagnosis, drug management, investigation, referral, initial advice, monitoring. Training in motivational interviewing and using appreciative inquiry

*Chronic disease detection*

*Chronic disease management*

Audit and feedback of aggregate data.

## Development and validation of a total cardiovascular risk assessment tool for developing countries

**Research question or hypothesis**

Calibrate and validate a non-laboratory based screening tool for cardiovascular disease (CVD) risk prediction in South Africa.

**Background and Significance**

The overall goal of this program of work is to develop a cost-effective screening strategy for those at high risk for cardiovascular disease (CVD) in low-income countries. Given the large global burden of CVD and very limited resources in developing countries, finding low-cost prevention strategies is a top priority. Screening to identify those at higher risk in order to target specific behavioural or drug interventions is a well-established primary prevention strategy.

During the 1970s numerous efforts were made to create models for predicting CVD risk using the associated risk factors by multivariate regression techniques. The most significant of these efforts was an equation derived from the Framingham cohort of both men and women aged 35 to 70 in the US. (Anderson, 1991) This logistic regression model used cholesterol, blood pressure, smoking history, an electrocardiogram and diabetic status to predict the 10-year absolute risk of a first time CVD event —fatal and nonfatal stroke, cardiac arrest, angina, and fatal and nonfatal myocardial infarction (MI). The current version eliminates the ECG. The WHO recently released guidelines for the prevention of CVD (WHO, 2007) that includes two risk charts for CVD. The first set of WHO charts use the same risk factors used in the Framingham risk equation but without HDL cholesterol. The second set of charts removes cholesterol and retains the remaining risk factors. However, the charts have not been validated in any of the WHO regions or countries—developed or developing. Further, given that the WHO charts were not based on a cohort with CVD outcomes, the investigators were not able to evaluate the predictive discrimination or calibration of either of their charts or make any comparisons between them.

Preliminary work in developed country cohorts has tested the hypothesis whether a non lab-based screening tool for cardiovascular disease could predict risk for CVD nearly as well as one that did require blood testing. We have found that in well characterized cohorts in the United States a simple screening tool that does not require lab testing can predict future CVD events as well as one that requires lab testing (Gaziano, 2008). This is important because a lack of financial, human and laboratory resources make lab testing impractical and costly in low resource settings. We compared two Cox models. The first is the “lab-based” model which requires blood testing and the second, which we designate as the “non lab-based” model, requires only history and physical exam measures. In both we compared how well either model could predict first time fatal and non-fatal CVD events in the NHANES I Epidemiologic Follow up Study (NHEFS) cohort. Both predictive models performed well in discriminating risk. In the women, the “lab-based” model performed well in predicting events with a C-statistic (95% confidence intervals) of 0.829 (0.813-0.845) The C-statistic of the “non lab-based” model was 0.831 (0.816-0.847). The test for significant difference between the two c-statistics is a chi-square result of 2.476 (p=0.116). Similar results were found for men. (Figure 2)

The next stage is to show that a screening mechanism using the same risk factors that does not require lab testing can also predict well in a different population. We also wish to test what is the most cost-effective and practical strategy for screening for CVD in South Africa. Therefore, the purpose of this proposal is continuing with the development of a simple risk prediction tool for CVD and to assess its cost-effectiveness in South Africa. Hopefully, the strategies can then be incorporated into national or international guidelines for the management of cardiovascular disease.

**Figure 2. ROC curves for lab and non lab-based CVD prediction tools.**

Women Men

**Design and Outcomes**

**Proposed Model Calibration Approach**

In this protocol, we seek to use various calibration techniques to adjust cardiovascular model inputs to result in model-predicted outcomes that fit the observed mortality data in South Africa. The calibration process will begin by evaluating the disease model populated with the transition probabilities previously used in South African modelling analyses, which were based on the Framingham risk equations (Gaziano *et al*, 2005) and compared to non-lab based measure. These inputs will be used to assess the initial fit of the model-predicted outcomes. During the calibration process, these model inputs will be adjusted so that the model outputs better reflect the observed endpoints from the regional/national database.

We will use several techniques to calibrate the parameters of interest and comment on the accuracy and efficiency of each approach. The technique of interest will be the Nelder-Mead/Downhill Simplex algorithm, which has been broadly used in engineering and physical science optimization problems, but less so in disease and cost-effectiveness models (Byatt *et al*, 2003). The Nelder-Mead algorithm attempts to minimize a non-linear function and is based on the simplex algorithm, which is compatible for calibrating complex disease models to observable clinical endpoints (Nelder and Mead, 1965). An advantage of this approach is that the Nelder-Mead algorithm has previously been found to be a relatively efficient method to calibrate a cervical cancer disease model compared to other calibration techniques (Taylor et al., 2007). However, to assess the robustness of the model results with respect to calibration methodology, we will employ two alternate calibration approaches and compare the results of each technique. The first of these options is to intuitively, or manually, adjust individual inputs without any formal algorithm. This approach is conceptually straightforward, but is subject to the biases and limitations of the analyst who conducts the manual calibration. The second alternative approach is to randomly vary the inputs of interest and evaluate the model results produced by each parameter set to the observed clinical endpoints. Since this approach relies on random sampling from probability distributions, it is less subjective than the manual approach. However, the random search algorithm is not efficient and can result in the evaluation of millions of parameter sets for complex models (Kim et al., 2007, Taylor et al., 2007).

To calibrate the risk score previously developed in the NHEFS cohort, we propose to use the South African Demographic Health Survey of 1998 (or Western Cape data) and the CVD morbidity and death rates from Central Statistics South Africa from 2003 and 2008 to recalibrate our lab-based screening tool for five and ten year predictions. We included the following risk factors in our analysis to compare a lab-based tool to a non-lab based tool, using the value closest to the entry date to the cohort for each patient: age (in single years); gender (men v women); smoking status (current smoker, non-smoker—including former smoker); systolic blood pressure (continuous); ratio of low density lipoprotein cholesterol to high density lipoprotein levels (continuous); body mass index (continuous); current prescription of at least one antihypertensive (yes or no), and diabetes status (yes or no). All data for this analysis is based on de-identified data sets. We will also use the DHS 98 and the relevant census data for validation of the WHO risk charts, using information on age, gender, smoking, blood pressure, and reported diabetes status.

The 1998 South Africa Demographic and Health Survey (SADHS) is the first survey of its kind to be carried out in South Africa since the 1994 democratic national elections. This national cross-sectional study collected information on adult health conditions; sexual, reproductive and women’s health; maternal and child health; adult, maternal, child and infant mortality; fertility and contraceptive use. Preparations for the study started in 1995 and the fieldwork was carried out between late January and September 1998.

They were also asked about recent contact with the health-care system, insurance status, family medical history, personal medical history, other medication use, smoking, occupational health, and lifestyle/habits. Information regarding other demographic factors such as age, education level and population group was also recorded.

The fieldworkers assessed anthropometric measurements, blood pressure, pulse rate, and peak expiratory flow rate on each participant at their home. Systolic and diastolic blood pressure and pulse measurements were taken 3 times with the patient seated and the left arm at the level of the heart after the participant was seated for 5 minutes. An Omron M1 electronic blood pressure manometer was used. In addition information on smoking status, diabetes status, medications for hypertension, and body-mass-index were collected and will be used in the calibration model. Population based means for these values with standard errors will be used to model death rates from CVD.

To assess calibration (the degree of similarity between observed and predicted risks) we will calculate the mean predicted risk of cardiovascular disease at 10 years and the observed risk at 5 years obtained using the 5 year Kaplan-Meier estimate. We then compared the ratio of the predicted to the observed cardiovascular disease risk for patients in the validation cohort in each tenth of predicted risk.

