**Risk Prediction Validation**

The calibration of the CVD risk score is important for national projections of disease incident and projections of future mortality based on changes in the various risk factors. However, for its reliable use in predicting individual risk, validation in prospective cohorts is ideal. CVD prediction charts for the different regions of the world that do not require lab testing have been suggested (Mendis *et al*, 2007; Lim *et al*, 2007) by the WHO but they have never been compared with any of the standard risk prediction rules or validated in any cohort. We will attempt to validate both the non-lab based prediction tool from our work in the NHEFS cohort as well as the WHO risk prediction charts.

To develop and validate a new score we will use the cohort of approximately 2000 patients described in the main programmatic trial outline below in a separate protocol who are over the age of 35 and without prior history of CVD. Our endpoint for censoring as described will be all cause mortality and CVD mortality encompassing the appropriated ICD codes for ischemic heart disease, stroke and hypertensive heart disease. Participants will also be asked to provide their South African identity number. This will be used to link with the national mortality register at 5 and 10 years from the start of the study. Unfortunately, data collection methods and resources do not allow for us to confirm non-fatal CVD events. We hope to eventually use this pilot data for use in a larger cohort to evaluate both morbidity and mortality data for a more refined risk scoring mechanism.

Therefore we propose to use the information from the cohort of patients enrolled in the cluster randomized control trial (described below) to validate the risk score. The initial evaluation will allow us to develop a risk score for total mortality. In the NHEFS cohort above, a risk prediction tool using non-lab based values had remarkable discrimination in predicting those at high risk for overall mortality with a C-statistic of 0.85 and 0.86 for women and men respectively. We will then test for predictive accuracy in predicting CVD mortality even though we recognize that there is likely to be some misclassification due to the incomplete death certification in South Africa.

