We included the following risk factors in our analysis to compare a lab-based tool to a non-lab based tool, using the value closest to the entry date to the cohort for each patient: age (in single years); gender (men v women); smoking status (current smoker, non-smoker—including former smoker); systolic blood pressure (continuous); ratio of low density lipoprotein cholesterol to high density lipoprotein levels (continuous); body mass index (continuous); current prescription of at least one antihypertensive (yes or no), and diabetes status (yes or no). Having calibrated the model from the national data we can then apply this data from this specific validation cohort. We calculated the 5 year estimated cardiovascular disease risk for each patient in the validation dataset. For development and validation of the new risk score we will use Cox proportional hazards regression to assess the “lab-based” model and compare it with the “non lab-based” model.

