2. Identified (ID number) data is available from the population register within about 3 months of the event with limited information on whether cause is natural or external. This data is restricted to deceased who are registered.

3. The Western Cape Provincial Government has extended a local level mortality surveillance system from 2 health districts to cover the province as of 2008. This will provide underlying cause of death as well as health sub-district and will be identifiable with ID. It will also include deceased who are not registered.

All mortality data will be stored by the Medical Research Council in keeping with existing agreements with the Department of Home Affairs and the Western Cape Department of Health.

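### The calibration check sets 10-year predicted CVD risk against 5-year observed risk, so a perfectly calibrated tool would show a ratio of about 2

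*Combined protocol and SAP*

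**What the plan says.** The check is defined once, at the end of Proposed Model Calibration Approach: it compares the "mean predicted risk of cardiovascular disease at 10 years and the observed risk at 5 years", the observed figure being a 5-year Kaplan-Meier estimate. The next sentence gives the statistic, "We then compared the ratio of the predicted to the observed cardiovascular disease risk for patients in the validation cohort", taken by decile of predicted risk. No rescaling to a common horizon is mentioned.

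Other places bear on it:

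- Risk Prediction Validation uses a different prediction horizon: "We calculated the 5 year estimated cardiovascular disease risk for each patient in the validation dataset".
- The same section plans the follow-up through the participant's identity number: "This will be used to link with the national mortality register at 5 and 10 years from the start of the study".
- Earlier in Proposed Model Calibration Approach, the recalibration to South African data is planned for both five- and ten-year predictions (the sentence names the lab-based tool).
- On the endpoint, the preliminary US work tested how well the models "could predict first time fatal and non-fatal CVD events" (Background and Significance). For the South African cohort, Risk Prediction Validation names all-cause and CVD mortality, and adds: "Unfortunately, data collection methods and resources do not allow for us to confirm non-fatal CVD events".

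**The concern.** The protocol describes calibration as how closely observed and predicted risks agree, so a ratio of 1 is the natural target. A 10-year risk is larger than a 5-year risk in the same people whenever events continue to occur after year 5. The ratio as defined therefore has a target well above 1, and that target depends on the level of risk and on how the hazard changes over time.

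The error can mislead in both directions. A sound tool would be reported as over-predicting about two-fold. A tool that predicts about half the true 10-year risk would be reported as well calibrated. Calibrating and validating the tool is the stated purpose of this component, and the Synopsis says the tool will go into later versions of the guideline once it is validated. A misleading calibration result therefore matters for how the tool is judged.

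**Working it through.** The plan gives no expected value for the ratio, so there is no figure to reproduce. The question is what ratio a perfectly calibrated tool would produce under the stated definition.

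**Inputs from the plan.** Numerator: predicted risk at 10 years. Denominator: Kaplan-Meier observed risk at 5 years. Statistic: numerator over denominator, by decile of predicted risk.

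**Assumptions.** The plan gives neither the 5-year risk in this cohort nor the shape of the hazard. I take 5-year risks (R5) of 1% to 20%. The hazard is constant in the base case, with falling and rising hazards as sensitivity cases.

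**Formulas.** For a perfectly calibrated tool the ratio is R10/R5.

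- Constant hazard: R10 = 1 − (1 − R5)², so R10/R5 = 2 − R5.
- Weibull, shape k: R10 = 1 − (1 − R5)^(2^k).
- Gompertz, growth g per year: R10 = 1 − (1 − R5)^(e^(5g) + 1).

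For example, with R5 = 5% and constant hazard, R10 = 1 − 0.95² = 9.75%, and 9.75/5 = 1.95.

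| R5 | Constant | Weibull k = 0.8 | Weibull k = 1.5 | Gompertz g = 5% | Gompertz g = 10% |
|---|---|---|---|---|---|
| 1% | 1.990 | 1.735 | 2.803 | 2.269 | 2.627 |
| 2% | 1.980 | 1.728 | 2.777 | 2.255 | 2.605 |
| 5% | 1.950 | 1.709 | 2.701 | 2.211 | 2.541 |
| 10% | 1.900 | 1.676 | 2.577 | 2.139 | 2.435 |
| 20% | 1.800 | 1.610 | 2.340 | 1.997 | 2.231 |

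The table runs from about 1.6 to 2.8, and no cell is near 1. Within each column the ratio falls as risk rises, so the distortion differs between deciles and cannot be removed by one constant.

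**The reverse case.** If the tool predicts half the true 10-year risk, the constant-hazard ratio is (2 − R5)/2: 0.99 at R5 = 2%, 0.975 at 5% and 0.90 at 20%. A two-fold under-prediction would pass as good calibration.

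**After matching horizons.** With 5-year predicted over 5-year observed, or 10-year over 10-year, a perfectly calibrated tool has an expected ratio of 1 in every decile, whatever the hazard shape.

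**The case against.** The strongest reply is that this is a drafting slip. Risk Prediction Validation calculates a 5-year risk for each patient in the validation dataset, and five-year predictions are planned elsewhere, so a matched 5-year comparison was probably intended. That is plausible, and it makes the repair easy. It does not remove the problem, because the ratio is defined only in Proposed Model Calibration Approach, and an analyst who follows that text gets the wrong answer.

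The second reply is that the endpoint is already handled. The model is to be fitted to observed mortality, population risk-factor values are to be used to model CVD death rates, and the cohort endpoints are all-cause and CVD mortality. Most of this stands. What remains is that the calibration sentence speaks only of cardiovascular disease risk and does not say which endpoint the predicted side uses.

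The third reply concerns cause of death. A reader might infer that CVD deaths cannot be identified, because the general Data analysis section describes population-register data "with limited information on whether cause is natural or external". The documents do not support that inference. The same list includes a Western Cape system with both identity number and underlying cause, and the plan never equates the population register with the national mortality register it links to. At most this is a matter of naming the source. The plan also acknowledges misclassification from incomplete death certification.

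**Conclusion.** The definition is wrong as written. Under constant hazard, a perfectly calibrated tool gives 2 minus the 5-year risk, so 1.98 to 1.80 for 5-year risks of 2% to 20%. The wider range of about 1.6 to 2.8 rests on the assumed hazard shapes and on 5-year risks of 1% to 20%. That the target is not 1 needs only that events occur after year 5. The effect is a wrong calibration result for the validation study; the trial's outcomes are not touched.

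Three stronger readings are tempting, but the documents do not support them.

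- A reader might infer that the tool would be recalibrated on this ratio, halving predicted risks and moving high-risk patients below treatment thresholds. The recalibration is fitted to regional or national mortality and morbidity data, not to this ratio, and comes before the tool is applied to the cohort. No treatment threshold is tied to this tool.
- A reader might add a further two- to three-fold inflation because the US models predicted fatal and non-fatal events. That needs an assumed fatal fraction, which the plan does not give, and a prediction left unadjusted to deaths, although the plan points largely at mortality.
- A reader might conclude that Kaplan-Meier must give way to a competing-risk estimator. The documents show no error of any stated size from this choice, and the point does not depend on it.

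**What to change.** In Proposed Model Calibration Approach, redefine the check as 5-year predicted against 5-year observed risk, and 10-year predicted against 10-year observed risk once the 10-year linkage is done, by decile of the matching prediction. Reconcile this with Risk Prediction Validation so that both sections state the same horizons.

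In the same sentence, state that predicted and observed risk refer to the same endpoint, either CVD death or all-cause death as named in Risk Prediction Validation, because non-fatal events cannot be confirmed.

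The cost is a wording change and the corresponding change to the analysis. No new data are needed: five- and ten-year predictions and linkage at 5 and 10 years are already planned.

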### Preliminary studies

Recently, the South African Hypertension Society adopted and revised its new guidelines [based on the JNC VI and VII guidelines]. As South Africa is a multi-ethnic country where epidemiologic and cost data were available, we therefore felt this provided a unique and timely opportunity to conduct a cost-effectiveness analysis comparing the two approaches to help inform the potential consequences of the various guideline choices for hypertension. The study compared six strategies for different thresholds for the initiation of drug treatment—two different blood pressure levels (160/95 and 140/90 mm Hg taken from the past and the newly proposed South African guidelines respectively), and four different levels of absolute CVD risk over 10 years (40%, 30%, 20% and 15% calculated using the Framingham risk function). All six of these strategies were also compared to one of no primary prevention treatment.

The results of this analysis which we previously showed as preliminary were published in *Circulation* (Gaziano, 2005). The four “absolute risk” strategies had the four lowest incremental cost-effectiveness ratios. The strategy of initiating antihypertensive therapy for those individuals with a predicted 10-year CVD risk > 40% had an incremental cost-effective (C/E) ratio of $700 per quality-adjusted year of life gained compared to no treatment. The “absolute risk of CVD > 30%”, “absolute risk of CVD > 20%” and “absolute risk of CVD > 15%” had C/E ratios of $1600, $4900, and $11,000 per QALY respectively. On the other hand both the 1995 South African guidelines and the new guidelines were more costly and resulted in fewer gains in quality adjusted life-expectancy than the “absolute risk of CVD > 15%” strategy, and were thus dominated by the less costly absolute risk treatment strategies in the cost-effectiveness analysis.

Table 2 compares the projections of morbidity and mortality from our model with the estimates from the available literature on South Africa. In general, the model was able to accurately project the number of deaths due to ischemic heart disease and stroke, the incidence of stroke and the overall direct cost of CVD.

| **Table 2. CVD Model Predicted and Actual Outcomes in South Africa** | | |
| --- | --- | --- |
| Outcome | Model Prediction | Published Reports (range) |
| Annual Death due to IHD | 12% | 5-13% |
| Annual Death due to Stroke | 14% | 8-16% |
| Stroke rate (per 100 000) | 323 | 100-500 |

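### The 5-year Kaplan-Meier estimate overstates absolute CVD death risk in the by-tenth calibration check, and the plan does not say which risk scale the predictions use

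*Combined protocol and SAP*

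**What the plan says.** Under Proposed Model Calibration Approach, the combined protocol and SAP assesses calibration by setting the "mean predicted risk of cardiovascular disease at 10 years" against "the observed risk at 5 years obtained using the 5 year Kaplan-Meier estimate". The result is read as the "ratio of the predicted to the observed cardiovascular disease risk for patients in the validation cohort in each tenth of predicted risk".

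Under Risk Prediction Validation, the plan states "Our endpoint for censoring as described will be all cause mortality and CVD mortality", with CVD mortality defined by codes for ischaemic heart disease, stroke and hypertensive heart disease. The same section concedes that "data collection methods and resources do not allow for us to confirm non-fatal CVD events". CVD death is therefore the only CVD event available in the cohort.

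Neither section, nor the mortality sources described under Data analysis, says how a death from another cause enters the CVD estimate. No competing-risk method is named. The tool itself comes from Cox models (Background and Significance), and the new score is also to be fitted by Cox regression (Risk Prediction Validation).

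**The concern.** A person who dies of another cause can no longer die of CVD. By default, Kaplan-Meier treats that person as censored, which amounts to assuming that they would have gone on to die of CVD at the same rate as those still alive. The result is a net risk: the risk of CVD death if nothing else could kill. It is higher than the proportion who actually die of CVD whenever other deaths occur before the horizon.

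Calibration is judged by tenth, and the gap grows with mortality. It is therefore widest in the top tenths, the patients whom a screening tool is meant to find. A calibration statement for absolute risk would be wrong in shape as well as in level. The all-cause endpoint has no competing event, so Kaplan-Meier is right there.

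**Working it through.** The plan states no observed risk, cohort mortality or precision for this check, so there is no figure to reproduce.

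**Inputs**
- CVD share of deaths, *s*. Table 2 (Preliminary studies) gives ischaemic heart disease 12% and stroke 14%, read here as shares of all deaths: 12 + 14 = 26%. The published ranges give 5 + 8 = 13% to 13 + 16 = 29%. A value of 50% is added as a sensitivity case, because Table 2 is national and has no row for hypertensive heart disease, which the endpoint includes.
- Five-year all-cause mortality, *D*. This is not in the documents; 10%, 20% and 30% are assumed.
- Patients per tenth: about 2000 / 10 = 200.
- Cause-specific hazards are assumed constant.

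**Formulas**
- Kaplan-Meier with other deaths censored: 1 - (1 - D)^s
- Cumulative incidence of CVD death: s × D

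| s | D | Kaplan-Meier | Cumulative incidence | Ratio |
|---|---|---|---|---|
| 0.26 | 10% | 2.70% | 2.60% | 1.04 |
| 0.26 | 20% | 5.64% | 5.20% | 1.08 |
| 0.26 | 30% | 8.86% | 7.80% | 1.14 |
| 0.50 | 20% | 10.56% | 10.00% | 1.06 |
| 0.50 | 30% | 16.33% | 15.00% | 1.09 |
| 0.13 | 20% | 2.86% | 2.60% | 1.10 |
| 0.13 | 30% | 4.53% | 3.90% | 1.16 |

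**Spread over tenths.** This needs a further assumption, a binormal score. With the C-statistic of 0.85 that the protocol reports for overall mortality (women, US cohort), 5% overall mortality and s = 0.26, mortality is 1.6% in the fifth tenth and 25.9% in the top tenth. The excess is 0.6% and 11%. With C = 0.70 and 10% overall mortality, the fifth and top tenths have 7.5% and 25.9% mortality, with an excess of 2.9% and 11%. The steeper pairing of C = 0.85 with 10% overall mortality puts 46.3% mortality and a 24% excess in the top tenth. Over the whole cohort the excess is 2-6% for mortality of 5-15%.

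**Sampling error in one tenth.** Expected CVD deaths at s = 0.26 are 200 × 0.052 = 10.4 (D = 20%) and 200 × 0.078 = 15.6 (D = 30%). The relative standard error is about 1/√10.4 = 31% and 1/√15.6 = 25%.

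**Effect on predicted/observed for a correct model** (s = 0.26, D = 20% and 30%)
- Absolute predictions against Kaplan-Meier: 5.20/5.64 = 0.92 and 7.80/8.86 = 0.88. The tool appears to under-predict.
- Net (Cox) predictions against Kaplan-Meier: 1.00 and 1.00. The tool appears perfect.
- Net predictions against cumulative incidence: 5.64/5.20 = 1.08 and 8.86/7.80 = 1.14. This is over-prediction of absolute risk, which the Kaplan-Meier comparison hides.

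**Horizon, for scale.** With 10-year predicted against 5-year observed risk, both net, a correct model gives 1 + (1 - D)^s. That is 1.94 at D = 20% and 1.91 at D = 30%.

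**The case against.** The strongest objection concerns the consequence. A reader might infer that Kaplan-Meier makes the tool look as if it under-predicts in high-risk patients and so leads to upward recalibration. The documents do not support that in general. The tool and the new score are Cox models, and a Cox risk of CVD that censors other deaths is on the same net scale as Kaplan-Meier. The plan also calibrates to South African death rates, but it does not say how rates become risks, so this does not settle the scale. It follows that changing only the observed side could create a mismatch where none existed. This objection stands, and it shapes the fix.

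The other objections stand in part:
- Table 2 is not about this cohort. Participants are 35 or older and free of prior CVD, patients whose acute or terminal illness precludes participation are excluded, and many are shared with a trial in chronic disease. Their CVD share of deaths may be higher than 26%, and higher still in the top tenths of a CVD score. Both would shrink the excess. A reader might also infer that Table 2 shows most deaths in this cohort to be non-CVD; it shows that only for national figures.
- Larger excesses can be computed at 10 years, but the calibration text specifies only a 5-year Kaplan-Meier estimate. Record linkage at 10 years is planned; a 10-year Kaplan-Meier calibration is not written down.
- Two other mismatches are likely to be larger and push towards apparent over-prediction: the 10-year against 5-year horizon, and a tool built for fatal and non-fatal events judged against deaths alone. Correcting them leaves the competing-risk problem in place.
- At 200 patients per tenth the bias cannot be seen in a single tenth. It is nonetheless systematic, and the plan treats these data as a pilot for a larger cohort, where it would not diminish.

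**Conclusion.** The point holds in limited form. As written, the observed CVD risk is a net quantity that overstates absolute CVD death risk. The direction is certain if other deaths are censored, which is what a standard Kaplan-Meier estimate does and what nothing in the plan overrides.

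The size is conditional on assumed mortality, an assumed CVD share and constant hazards. The relative excess is about 4% at 10% five-year mortality and 8-14% at 20-30% with a 26% share, or 6-9% at 20-30% with a 50% share. It is small in the lower tenths.

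The effect on the predicted/observed ratio cannot be signed until the prediction scale is stated. Either the tool appears to under-predict in the top tenths, or over-prediction of absolute risk is concealed. The all-cause evaluation and the cluster trial's outcomes are not affected.

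**What to change.** In the calibration paragraph of Proposed Model Calibration Approach:
- For CVD death, estimate observed risk by the Aalen-Johansen cumulative incidence, with non-CVD death as a competing event.
- State that predictions are for the same endpoint (CVD death), on the same absolute-risk scale and at the same horizon. For Cox predictions, this means combining the cause-specific models for CVD and non-CVD death.
- Report the Kaplan-Meier comparison, with net predictions, as a secondary analysis.
- Keep Kaplan-Meier for all-cause mortality.

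The cost is a few sentences and some extra analysis to put predictions on the absolute scale. No further data are needed, because any estimate of CVD death already requires a coded cause. Under Data analysis, the provincial surveillance system supplies this, whereas the population register comes "with limited information on whether cause is natural or external".
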